### Software and reproducibility

All analyses will be conducted using reproducible statistical workflows in R and RStudio, with additional software used for meta-analytic synthesis where appropriate. Analysis scripts and documentation will be shared in open repositories where permitted, in line with FAIR principles and Open Science guidelines.

### Patient and Public involvement (PPI)

Patient and public involvement will be integrated to ensure that outcome interpretations and dissemination plans reflect the patient’s priorities and are communicated in accessible language. Therefore, we will establish a panel including people with lived experience of psychosis/schizophrenia recruited through a clinic network in Ireland. The panel will meet 3–4 times for approximately 60 minutes via online sessions supported by brief material. Participants will be remunerated as per institutional policy. PPI provided input will include structured discussions and written feedback in (i) plain-language summary, (ii) framing of “clinically meaningful change” for PANSS/BPRS on an individual level, (iii) planned subgroup analysis reporting and equity implications, and (iv) dissemination formats. Results will be reported according to the GRIPP2 short form checklist.
^
45
^

## Discussion

Advanced psychometric methods are widely advocated in the methodological literature as tools to improve measurement quality in clinical research.
^
46,
47
^ Yet, it remains uncertain whether they change what matters most – the estimated efficacy of interventions. This protocol is designed to test that practical question in schizophrenia research by quantifying whether psychometrically-informed scoring substantially alters antipsychotic treatment effect estimates.

Doyle et al. proposed,
^
19
^ and Byrne and colleagues subsequently demonstrated
^
13
^ that applying psychometric refinements can yield detectable differences in estimated antidepressant treatment effects, with the most consistent changes observed for factor-analytic approaches, while IRT- and network-based variants often produced little added value or inconsistent shifts in effects. The present project directly builds on this framework by translating it into schizophrenia trials, where measurement challenges and modest effects are long-standing concerns. Meta-analytic evidence from placebo-controlled antipsychotic drug trials have shown limited improvement across decades, suggesting that increasing placebo response is one plausible contributor to diminished effect sizes.
^
17
^ If placebo response grows (or baseline severity declines), detecting drug effects becomes more difficult, even when drugs remain efficacious, making it especially important that outcome measurement is as informative and low-noise as possible. Simultaneously, the interpretability of outcomes depends on the measurement properties of the instrument. A recent synthesis by Geck and colleagues concluded that the PANSS shows adequate performance regarding responsiveness and reliability, but has notable shortcomings in content validity and structural validity.
^
6
^ These limitations can weaken confidence in what total and subscale scores represent and how changes should be interpreted.

In this context, psychometric re-modelling using pooled IPD may help clarify which symptom structures replicate reliably, which items contribute meaningfully, and whether abbreviated scales will capture the same responsiveness to treatment or whether weighted scoring yields more accurate estimates of change. Importantly, we do not claim that psychometric refinement necessarily produces clinically meaningful change at the individual level. Rather, the planned analysis evaluates whether relatively modest differences in effect size (e.g., ~10–15% as observed in prior IPD psychometric work) are detectable and may improve the precision, interpretability, or comparability of trial effect estimates. Yet, they can still matter for meta-analytic synthesis, trial power, and the likelihood of detecting true treatment differences under challenging conditions.

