**Method:**

We will conduct secondary analyses of anonymised individual participant data from randomized Phase II–IV schizophrenia trials accessed via secure data-sharing platforms (YODA Project and Vivli). Item-level PANSS/BPRS data will be harmonised at baseline and outcome. Psychometric models will be derived using confirmatory factor analysis, item response theory, and network analysis. Stability and invariance analyses will be conducted, examining covariates such as age and sex. Antipsychotic efficacy will be estimated using mixed-effects participant-level models, expressed as Cohen’s d standardised mean differences (SMDs) for both conventional and psychometrically-informed outcomes. The primary outcome will be the difference in SMDs between conventional and psychometrically-informed effect sizes, summarised across trials.

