### Setting, participants and eligibility criteria

This study is open to randomized controlled multi-arm trials (Phase II-IV) comparing the effects of pharmacological treatments with antipsychotics to placebo (primary outcome) or any comparator (sensitivity analysis). Individual trial size is not an eligibility criterion. Eligible trials will include adult participants diagnosed with schizophrenia, schizoaffective or schizophreniform disorders. Trials must include PANSS and/or BPRS individual participant data at baseline and outcome. Studies meeting the criteria described in
Table 1 have been requested from
vivli.org (Vivli) and
yoda.yale.edu (YODA Project). Requested studies from the YODA Project are solely sponsored by Johnson & Johnson. In addition, Vivli provides data from the following sponsors: Abbott, AbbVie, Janssen, Johnson & Johnson, Lilly, Otsuka. Previous data checks suggests that we should expect to obtain a pooled sample of ~31 000 participants from 77 studies provided on the Vivli platform (
Table 2).

**Table 1. T1:** Inclusion/exclusion criteria for selecting trials and participant data.

Variable	Inclusion criteria
Study Type	Randomized controlled multi-arm trial
Data Type	Individual Participant Data
Phase	II, IIa, IIb, III, IIIa, IIIb, and IV
Population/Diagnostic Criteria	Participants with Schizophrenia Spectrum Disorders, aged 18 years and older
Treatment	Antipsychotic medication
Comparator	*Placebo* (to establish efficacy) *Active Comparator* (to establish baseline psychometric model)
Active Comparator	*Primary* (standard) *:* first-generation vs second-generation antipsychotics (optionally adding D2 partial agonists as a third category where feasible). *Exploratory:* receptor-based taxonomy as proposed by McCutcheon et al. ^ 21 ^
Outcome	Positive and Negative Syndrome Scale (PANSS) and/or Brief Psychiatric Rating Scale (BPRS)
Covariates	Sex (if available: Age)
Moderator Variable	Sex Stage of illness (sensitivity analysis)
Timing of Outcome Assessment	6 weeks, as per Younis et al. ^ 22 ^/ *4 weeks for sensitivity analysis*

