### Primary analyses: Continuous outcomes

For each instrument (PANSS and BPRS), outcome symptom severity will be modelled as a function of treatment assignment, adjusting for baseline symptom severity and accounting for clustering of participants within trials via random intercepts, as per best practice RCT modelling.
^
41
^ Detached from the psychometric modelling approach (CFA, IRT, NA) in Model 1 the overall effects of antipsychotics versus placebo, using conventional scoring (i.e., original raw scores) will be estimated. Model 2 comprises a set of related models that mirror Model 1, where raw scores are replaced with abbreviated sum scores based on the results of the psychometric analysis from stage 1. In Model 3 psychometrically-informed (weighted) scores, that are derived from the abbreviated models will be established. Model 2 and 3 will be calculated for each psychometric method separately (CFA, IRT, NA). Models 4, 5 and 6 will extend Models 1, 2a-c and 3a-c, by additionally adjusting for participant level covariates:
•Model 1 (conventional scoring): Outcome is the raw total score with treatment group and baseline score as covariates and a random intercept for trial.•Model 2 (abbreviated total scores): Outcome is a simplified total score created after removing redundant items (as per relevant psychometric method) treatment group and corresponding baseline abbreviated score included as a covariates and a random intercept for trial.oModel 2a – factor analysis abbreviated total scoreoModel 2b – IRT abbreviated total scoreoModel 2c – NA abbreviated total score•Model 3 (weighted psychometric scores): Outcome is a psychometrically derived score (e.g., factor score, IRT expected score, or net score) treatment group and corresponding baseline abbreviated score included as a covariates and a random intercept for trial.oModel 3a – factor analytic weighted scoresoModel 3b – IRT weighted scoresoModel 3c – NA weighted scores (net score)•Model 4: Model 1 additionally adjusting for participant-level covariates (e.g. sex, age [where available])•Model 5a-c: Model 2a-c additionally adjusting for the same participant-level covariates•Model 6a-c: Model 3a-c additionally adjusting for the same participant-level covariates

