Effect estimates from each model will be transformed into Cohen’s d to facilitate comparison across trials and scoring approaches. The primary effect of interest is the difference between SMDs derived from those derived from conventional scoring and psychometrically-informed outcomes (i.e. Model 1 vs Models 2a-c vs Model 3a-c, and Model 4 vs 5a-c vs Model 6a-c).

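### The primary SMD comparison has no equal-length benchmark, so a detectable difference alone cannot be credited to psychometric refinement rather than to having fewer items

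*Protocol article*

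**What the plan says.** The abstract fixes the outcome: "The primary outcome will be the difference in SMDs between conventional and psychometrically-informed effect sizes, summarised across trials". The section on primary analyses of continuous outcomes repeats it ("The primary effect of interest is the difference between SMDs derived from those derived from conventional scoring and psychometrically-informed outcomes") and lists the contrasts: Model 1 against 2a-c against 3a-c, and Model 4 against 5a-c against 6a-c.

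For Model 2, "Outcome is a simplified total score created after removing redundant items". Model 3 uses weighted scores that the same section derives from those abbreviated models. Every refined score therefore rests on a reduced item set.

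The Stage 2 heading asks whether psychometric modelling matters. The Discussion describes the aim as "quantifying whether psychometrically-informed scoring substantially alters antipsychotic treatment effect estimates" and later says that "the planned analysis evaluates whether relatively modest differences in effect size (e.g., ~10–15% as observed in prior IPD psychometric work) are detectable". No direction, margin, test or null value is attached to these statements. On size, the eligibility section says "we should expect to obtain a pooled sample of ~31 000 participants from 77 studies provided on the Vivli platform", but the primary outcome uses placebo comparisons only, and the placebo-controlled share is not given.

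**The concern.** Each refined score differs from the conventional total in two ways: it has fewer items, and it has these particular items or weights. The difference between Model 1 and Model 2 combines the two, and no planned model separates them.

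Zero is not the value to expect when the psychometric selection adds nothing. A sum of fewer, equally informative items is less reliable, so its SMD falls even if the drug acts identically on every item. The short and full scores are also highly correlated within participants, so their difference has a small standard error in a large pooled sample and small mechanical shifts can be detected.

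At stake is attribution. The study is meant to inform the choice of outcome measure, and a detectable change could be credited to factor analysis, IRT or network selection when an arbitrary short form of the same length would have produced it. Inspecting the drug effect on the removed items would not settle this, because the fall occurs with equal effects on all items.

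**Working it through.** **The plan's own figures.** The 10–15% is given as an example from earlier work, with no power, alpha or standard error, so there is nothing to reproduce. The Vivli study counts add up (1 + 1 + 9 + 26 + 36 + 4 = 77).

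**Inputs.** From the protocol: PANSS has 30 items. Assumed: 20 items kept, inter-item correlation ρ = 0.2, mean item effect δ = 0.2 SD, equal arms, two-sided alpha 0.05, N = 3,000, 10,000 or 20,000 in placebo comparisons, and no between-trial variation in the difference.

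**Step 1: mechanical fall.** With equal effects on all items, the SMD of a k-item sum is δ·√(k/(1+(k−1)ρ)).
- k = 30: 0.2 × √(30/6.8) = 0.2 × 2.100 = 0.420
- k = 20: 0.2 × √(20/4.8) = 0.2 × 2.041 = 0.408
- Difference −0.0118; ratio 2.041/2.100 = 0.972, a fall of 2.8%

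The same formula gives falls of 1.2% for 25 items, 5.4% for 15 and 10% for 10.

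**Step 2: correlation of the two sums.** The covariance is 20 × (1 + 29 × 0.2) = 136. The SDs are √(30 × 6.8) = 14.28 and √(20 × 4.8) = 9.80. So r = 136/(14.28 × 9.80) = 0.972.

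**Step 3: standard error of the paired difference.** Var = (4/N)·2(1−r) + (d²/N)(1−r²), with d² ≈ 0.172 (mean of the two squared SMDs).

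| N | SE | z = 0.0118/SE | Significant against zero |
|---|---|---|---|
| 3,000 | 0.0089 | 1.34 | 27% |
| 10,000 | 0.0049 | 2.44 | 68% |
| 20,000 | 0.0034 | 3.45 | 93% |

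With equal item effects, the expected shift is always a loss.

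**Step 4: unequal item effects.** Simulated random 20-item subsets, with item effects of mean 0.20 and SD 0.10 (coefficient of variation 0.5):
- mean change −2.8%
- loss above 10% in about 13% of subsets, gain above 10% in about 2%
- significant gain of any size in about 15%, 21% and 24% at N = 3,000, 10,000 and 20,000

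With item-effect SD 0.05, a loss above 10% occurs in about 1% and a gain above 10% almost never.

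**Step 5: other assumptions.** With 2:1 allocation, d = 0.4, single or block correlation structures, PANSS cut to 25, 20, 15 or 10 items and BPRS cut from 18 to 14 or 10, a random short form differs significantly in either direction in 12–75% of cases at N = 3,000 and 29–99% at N = 10,000. For 20 of 30 items, a gain of 10% or more occurs in 0–2% of subsets for a coefficient of variation up to 0.5, and in 7–16% at 0.75–1.0.

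**Step 6: between-trial variation.** Suppose 30 placebo trials and a between-trial SD of 0.02 in the difference (both assumed). At N = 10,000, using the first variance term only (SE 0.00475, detection about 70%), the SE becomes √(0.00475² + 0.02²/30) = 0.0060 and detection drops to about 51%. With an SD of 0.05 the SE is 0.0103 and detection about 21%.

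**The case against.** The strongest reply is that the protocol asks a practical question: does the refined score give a different effect from the conventional total? The loss from shortening is part of what a user of the short score would experience, and for that question zero is the right reference. This stands. It does not cover the further step of crediting the change to refinement, which the Stage 2 heading and the Discussion's interest in precision invite.

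A reader might infer that the plan commits to a test against zero. It does not: no test or null is written, and its criterion words are about meaningful or substantial change.

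A reader might also infer that the comparison cannot distinguish refinement from random item removal at all. The numbers do not support that. Random shortening mostly lowers the SMD, and a gain in the 10–15% range would be uncommon by chance unless item effects differ very strongly. Nor does the text support the idea that a short scale keeping the full SMD would be reported as no gain, since the Discussion asks whether abbreviated scales retain the same responsiveness.

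Two further points stand. Model 3 against Model 2 is already a length-matched contrast, though it isolates weighting and not item selection. The detection rates rest on inputs that the document does not give, and between-trial variation would lower them.

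An unseen analysis plan might add a benchmark. However, the article's own statistical section enumerates the models and defines the primary contrast, and none of those models is an equal-length comparator.

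**Conclusion.** The point holds in a limited form. The primary comparison mixes shortening with psychometric selection and has no equal-length benchmark, so a detectable difference alone, especially a loss or a small shift, cannot be attributed to refinement. For 20 of 30 items with equal item effects, the mechanical fall is 2.8%, detected in about 27%, 68% and 93% of cases at N = 3,000, 10,000 and 20,000. These rates assume an inter-item correlation of 0.2, a mean item effect of 0.2 SD, equal arms and no between-trial variation in the difference. The placebo-controlled N is not stated. A gain above 10% is much harder to explain by chance: about 2% of random subsets at item-effect SD 0.10. This is an inexpensive improvement to attribution that should be made; it does not invalidate the planned analysis.

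**What to change.** Keep all planned differences, and keep zero as the reference for whether scoring changes the estimate.

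For each abbreviated score in Models 2a-c and 5a-c, also refit the model on several hundred random item subsets of the same length from the same scale. Report where the refined score's signed SMD difference falls in that distribution, and attribute a change to psychometric selection only when it lies outside the reference range. State that range and the direction of interest in advance.

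For Model 3, use the contrast with Model 2 on the same items to isolate weighting, or rescore random same-length subsets with the same method. Permuting item weights is not suitable, because IRT latent trait scores are not linear item weights.

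The item-level data will already be in the secure environment. The cost is extra computing, a paragraph in the protocol and more cautious wording of some differences.

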### Limitations

Several limitations should be acknowledged. Our planned analysis relies on available trials within controlled-access repositories: Hence, data might vary regarding follow-up timing, inclusion criteria, and data completeness, which may influence both psychometric models and effect size estimates. Psychometric BPRS and PANSS modelling across heterogeneous trials may yield more than one statistically defensible solution. We will therefore prioritise transparency in model comparison and report repository-specific results. Psychometric refinement may improve measurement in some contexts, but not in others. Data user agreements with Vivli and YODA Project may limit sharing of IPD and restrict reproducibility to code/scripts and permitted metadata, rather than full data transparency.

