### Stage 1: Establishing optimal psychometric models of PANSS and BPRS

### Exploratory and Factor analytic approaches

Data will be randomly split into exploratory and confirmatory datasets, as recommended by Lubke and Luningham,
^
27
^ with stratification by treatment group and trial to ensure balanced representation. For stratification and subsequent subgroup/invariance checks, active antipsychotic arms will be coded using literature-standard classification (primary approach: first-generation vs second-generation antipsychotics; where feasible, a third category for D2 partial agonists may be considered). In exploratory analyses, we will additionally code active agents using McCutcheon and colleagues’ data-driven receptor-based taxonomy,
^
21
^ namely muscarinic (M2-M5) receptor antagonists; dopamine (D2) partial agonists and adrenergic antagonists; serotonergic and dopaminergic antagonists; and dopaminergic antagonists. We will ascertain factor models of schizophrenia for baseline (pre-treatment), combined outcome (post-treatment; 6 weeks) and separately for placebo and treatment groups. We will further evaluate measurement invariance across major arm categories (e.g., placebo vs active treatment and, where supported, across active treatment-arm classes) within the best-fitting baseline model(s).

Parallel analysis will be applied to the exploratory datasets to determine symptom dimensionality.
^
28
^ Next, the EFA will be performed, using oblique rotation to allow for correlated symptom domains, to examine the factor structure of the exploratory dataset. Models will be refined iteratively by evaluating factor loadings below 0.3 and/or communalities below 0.4, with poorly performing items removed where justified to achieve stable and interpretable solutions.
^
29
^

In the confirmatory dataset, CFA will be used to formally test candidate psychometric models identified during the exploratory phase. In addition to simple structures derived from EFA, established alternative models, including higher-order and bifactor representations, will be evaluated.
^
30

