^ To select the optimal model of schizophrenia, the selection process will be guided by established absolute and relative fit indices, information criteria, and internal consistency metrics, including: the Root Mean Square Error of Approximation (RMSEA; < 0.08), Standardised Root Mean Square Residual (SRMR; < 0.08), Comparative Fit Index (CFI; > 0.95), Tucker-Lewis Index (TLI; > 0.95), Akaike Information Criterion (AIC), Bayesian Information Criterion (BIC), and McDonald’s Omega (acceptable >0.70), following established practices.
^
31,
32
^ Similar to the exploratory approach, confirmatory modelling will be performed for baseline and for the primary post-baseline outcomes. For outcome (post-baseline) measurement models, we will estimate the best-fitting model in the pooled sample and then test invariance across key arm categories (placebo vs active; and where feasible across active-arm classes as defined by the standard classification, with McCutcheon’s taxonomy explored in sensitivity analyses). We will retain the best-fitting baseline and post-baseline model(s) to derive factor scores for downstream treatment-effect estimation in Stage 2.
^
33
^

Measurement invariance, i.e. metric invariance (factor loadings are equal) and scalar invariance (intercepts are equal) across sex will be assessed, and differential item functioning examined by mean, standard error, standard deviation, factor loading scores and
*r
^2^
* values. When invariance is violated, psychometrically optimized models will be examined separated by sub-group (e.g., women and men).

The outcomes of these analyses will then be used for further evaluation and discussion (descriptively) on their differences or similarities in all models and datasets. This procedure will include model structure or item functioning (i.e. dropped items, item loadings on factor). Revised sum scores based on the retained items and weighted scores will then be computed from the best performing baseline and combined outcome model for each measure. These will be used for the stage 2 analysis described in the following sections.

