### Network analytic approaches

Network analysis is a more recent approach to psychometrics, which differs from traditional theories in that it does not assume that symptoms are caused by a single underlying latent trait. Instead, NA conceptualises symptoms as mutually interacting components, represented as a graph in which nodes are symptoms and edges reflect conditional associations between symptoms.
^
38,
39
^ This perspective has been proposed as a clinically intuitive complement to traditional models of psychopathology. Using best practice approaches, we will estimate empirical network structures separately for baseline (pooled across arms) and outcome data (separated by treatment arm). Network analysis will follow an exploratory graphical workflow, to identify the dimensional structure and detect redundant or weakly-performing items. As recommended by Christensen and Golino,
^
40
^ bootstrap-based stability assessment will be applied and empirical networks will be assessed in relation to the bootstrapped samples. Their work also suggests that replication metrics around the ~0.65–0.75 range mark the point at which variables begin to show reduced stability, providing a practical basis for identifying potentially unstable items.
^
12,
40
^ A key goal is to identify a network structure that is stable and configurally invariant across baseline and outcome (or treatment arms). If invariance cannot be achieved, we will proceed with the network solution with fewest/least consequential instabilities. From the final network solution, we will compute (i) revised sum scores based on the retained items, and (ii) weighted “net scores” derived from network loadings/strength. A detailed description of the analysis principles for the NA approach is outlined in Byrne’s publication.
^
15
^

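### The protocol expects several defensible PANSS/BPRS solutions, but its remedy does not show whether a rival solution from the same method would change the primary SMD difference

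*Protocol article*

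**What the plan says.** The Limitations section states that "Psychometric BPRS and PANSS modelling across heterogeneous trials may yield more than one statistically defensible solution". Its response is: "We will therefore prioritise transparency in model comparison and report repository-specific results".

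Stage 1 narrows each method towards one scored solution:

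- **Factor analysis.** Besides the structures found by EFA, "established alternative models, including higher-order and bifactor representations, will be evaluated". Scores are then "computed from the best performing baseline and combined outcome model for each measure". One sentence in the same section is looser: "We will retain the best-fitting baseline and post-baseline model(s) to derive factor scores".
- **IRT.** Mokken solutions are compared over a grid of scalability thresholds, and one is chosen for interpretability.
- **Network.** If invariance fails, "we will proceed with the network solution with fewest/least consequential instabilities". Both scores come from the final network.

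Stage 2 (Primary analyses: Continuous outcomes) lists Models 2a-c and 3a-c, which is one abbreviated and one weighted score per method. The primary effect is the SMD difference between these and Model 1. The planned repeat analyses concern sex, endpoint timing and stage of illness. The Discussion says that the study looks for "relatively modest differences in effect size", of about 10-15%.

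**The concern.** The study asks whether the choice of scoring alters the estimated drug effect. If a method has several acceptable keys (item lists and weights) and only one is scored, a shift that belongs to that key can be reported as the effect of factor analysis, IRT or network scoring.

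The choice also leaves room for judgement. Low-loading items are dropped if removal is thought justified, the Mokken solution is chosen for interpretability, and the network is chosen by how consequential its instabilities are. The several CFA fit indices have no order of precedence. Meanwhile the analysts fit factor models separately for placebo and treatment, and outcome networks by arm. The protocol does not say that the keys are fixed before treatment effects are estimated.

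**Working it through.** **1. Does the stated remedy reach the primary outcome?**

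- *Model comparison.* The factor-analysis section describes it as descriptive and as covering model structure and item functioning. SMDs are not mentioned.
- *Repository-specific results.* Table 2 gives Vivli 1 + 1 + 9 + 26 + 36 + 4 = 77 and YODA 26 + 36 = 62; both totals reproduce. All 62 YODA studies are on Vivli (62/77 = 80.5%), which leaves 77 - 62 = 15 Vivli-only studies. This split changes which trials are analysed, not which key is used.
- *Number of keys.* There are three methods with two scores each, so six refined scores per instrument. None is a rival within a method. The Mokken grid alone has 1 + 12 = 13 thresholds (0.01, then 0.05 to 0.60 in steps of 0.05).

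**2. How far apart could two keys be?** The 10-15% has no inputs in the protocol and cannot be reproduced. All item-level figures below are assumptions.

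*Simple model.* Inter-item correlation r = 0.25, mean item SMD 0.30, item SMDs varying with SD s. The SMD of a k-item sum is Σd / √(k(1 + (k-1)r)).

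- Full 30 items: 9/√247.5 = 0.572.
- Two 20-item keys that differ in 4 items: SD of the gap = s√8/√115. At s = 0.10 this is 0.026, or 4.6% of 0.572. At s = 0.05 and 0.15 it is 2.3% and 6.9% (7.1% by simulation).
- Two 12-of-18-item keys that differ in 3 items: full-scale SMD 5.4/√94.5 = 0.556; SD of the gap = s√6/√45, giving 3.3%, 6.6% and 9.9%.

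*Three-factor model.* PANSS-like, 7/7/16 items, SMD = w'e/√(w'Sw). Mean loading 0.6 (SD 0.13), factor correlation 0.3 or 0.5. Each key keeps the items with the highest noisy loadings (noise SD 0.1). Ranges run from equal domain effects (0.45 each) to strongly unequal ones (positive 0.7, negative 0.2, general 0.35).

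| Items kept | Median gap, % of SMD | 90th percentile | Share of draws ≥10%, equal effects | Share ≥10%, strongly unequal |
|---|---|---|---|---|
| 25 | 0.5-3 | 1.3-6.7 | 0% | about 1% |
| 20 | 0.8-5 | 2-10.5 | 0% | 9-13% |
| 12 | 1.3-8 | 4-18.5 | 0-1% | 29-33% |

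*Fixed example.* All loadings 0.6, factor correlation 0.3, strongly unequal effects. Full scale: 7.14/√205.6 = 0.498. A 20-item key split 7/3/10 (positive/negative/general) gives 5.40/√95.8 = 0.552, or +11%. A 4/6/10 key gives 4.50/√94.3 = 0.463, or -7%. The spread is about 18 points and the sign changes. With equal domain effects the same two keys differ by under 1 point.

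**3. Against sampling error.** For two scores on the same participants with score correlation ρ, the 95% half-width is about 1.96√((4/N)·2(1-ρ)) under equal allocation. At ρ = 0.95 it is 0.007 for N = 31 000 (an upper bound, since not every trial has a placebo arm) and 0.018 for N = 5 000. A 4-5% gap on an SMD near 0.5 is 0.020-0.025, which is larger. With equal domain effects and 20 items kept, the median gap is 0.008 × 0.518 = 0.004 to 0.013 × 0.565 = 0.007, which is not larger.

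**4. Against the effect sought.** On assumed SMDs of 0.3, 0.4 and 0.5, 10-15% is 0.030-0.045, 0.040-0.060 and 0.050-0.075. The typical gaps at 20 items are below these ranges.

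**The case against.** The best defence is that this is an openly stated limitation in a journal article, and that robustness checks over near-equivalent models commonly sit in a fuller plan. There are also real safeguards. Stage 1 precedes Stage 2, data are split into exploratory and confirmatory sets, CFA selection uses numeric fit criteria rather than SMDs, three methods are reported side by side, trial-level differences are estimated, and psychometric parameters and code are to be shared where permitted.

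Much of this stands, and it limits the point. It does not remove it: the article names the ambiguity, states a response and lists the Stage 2 models, and that response stops short of the primary outcome. Three methods side by side show variation between methods, not within one.

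Several stronger readings are not supported:

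- *That the choice of key moves the answer as much as the effect sought.* No figure in the protocol shows this. In the simple model the PANSS gaps have SDs of about 2-7%, and under equal domain effects they can be under 1 point.
- *That the reported interval will be too narrow.* The protocol describes no interval for the SMD difference.
- *That only one factor model can enter Stage 2.* One sentence allows more than one. The scoring sentence and Models 2a and 3a do not carry that through.
- *That keys will be picked for a favourable result.* Nothing says so. The point is only that nothing rules out influence from arm-separated outcome data.

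The calculations also swap items in sum scores. Higher-order and bifactor models may share an item list, in which case only the Model 3a weights would differ, and that case was not computed.

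**Conclusion.** The point holds as a gap between a named problem and its remedy. As written, a reader could not tell whether a reported shift belongs to a method or to one of that method's acceptable keys. On the illustrative assumptions, two keys of equal standing differ by anything from under 1% to several percent of the SMD. This can exceed the sampling error of the paired difference. It approaches 10-15% only when the retained sets are short or differ in domain mix and the drug effect also differs by domain. The textual part needs no assumption; the size rests entirely on assumed loadings, item effects, numbers of items kept and score correlations. It is worth correcting before Stage 2 starts, but it does not invalidate the design.

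**What to change.** 1. Before any Stage 2 model is fitted, deposit time-stamped item lists and weights for the lead solution and its rivals on the OSF page that the study already uses.
2. Keep the selected solution as lead. As a sensitivity analysis, repeat the unadjusted primary comparison (Models 2 and 3 against Model 1) for the rivals. For CFA, these are the other models that meet the stated cut-offs (RMSEA and SRMR below 0.08, CFI and TLI above 0.95, omega above 0.70). For IRT and network, use one alternative each, named in the deposit, such as the solution at an adjacent Mokken threshold or a runner-up stable network.
3. Report the range of SMD differences within each method, and word the conclusion as model-dependent if the sign changes.

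Cost: no new data. With m rival CFA models, there are at most 2(m + 2) extra fits per instrument beside the six planned (six if m = 1, eight if m = 2), and fewer where rivals share an item list. Covariate-adjusted, trial-level and response analyses need not be repeated. The downside is a longer results table and a possibly less clear-cut headline.
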